### Project Title

Scientific title: ALzheimer and MUsic THerapy: Randomised trial of Singing Lessons versus Exercise or No Treatment on Brain Age and Depression Symptoms in People with Alzheimer Disease (ALMUTH)

Short title: ALzheimer and MUsic THerapy: Trial of Singing Lessons for People with Alzheimer  
Acronym: ALMUTH, which stands for ALzheimer and MUsic THerapy.

### Trial Registration

The project was released to ClinicalTrials.gov for review on February 16, 2018.

### Funding

The project is funded by Norsk Forskningsråd and the Institute of Biological and Medical Psychology (IBMP) at the University of Bergen (UiB). The authors declare that they have no conflicts of interest. The funder will not have any role in the design or conduct of the study, in the writing of the report, or in the decision to submit the report for publication.

## **Abstract**

Music has powerful effects on memory in patients with neurodegenerative diseases. However, although there is anecdotal evidence for beneficial effects of active music interventions in patients with Alzheimer's disease (AD), there is lack of high-quality research investigating this issue, and the cognitive, emotional, and social factors that contribute to potentially beneficial effects of music making in AD patients are largely unknown. In a randomised controlled intervention trial, a cohort of AD patients will undergo twelve months of music lessons specifically tailored for AD patients. Another group of AD patients will undergo twelve months of exercise lessons and a third group of AD patients will be in a passive control group. Structural and functional magnetic resonance imaging (MRI) will be used to determine changes in brain age (as compared to two control groups), and voxel-based morphometry will be computed to determine contributions of different factors of the music intervention (cognitive, emotional, and social) to plastic changes of brain morphology, and a potential deceleration of brain atrophy. In addition, quality of life of patients. In cooperation with the Bergen municipality, and a strong network of national and international partners, music therapy will be implemented, involving training of music therapists, and communication of results to patients, patient groups, and therapists.

## **Introduction**

### **Background**

Alzheimer's disease (AD) (Selkoe, 2001) is a neurodegenerative disease where patients experience a worsening of episodic and semantic memory, cognitive functions and language. Behavior is also affected by the disease as a result of loss of norm understanding, paranoia and delusions. Selkoe and Dennis (2001) points out that AD symptoms may be improved with medicine, but there is no cure for AD.

According to figures from the Norwegian Institute a Public Health Report from 2014, every fifth person in Norway will develop dementia during their lifetime. Furthermore, in the 2014 report, 42 000 people in Norway will get AD, which is the most common form of dementia.

A literature study (Hulme, Wright, Crocker, Oluboyede, & House, 2010) examined 33 literature reviews on non-medical treatments of dementia. In their survey they identified music or music therapy as the strongest, most efficient non-drug treatment of dementia. The authors further pointed out that music was efficient for calming people with dementia and hindered wandering. Exercise was identified as the second most effective treatment of dementia in this literature review. The studies all tested dementia patients in later stages of the disease (not persons who still lived at home).

Singing and music interventions can have several benefits in themselves. One study (Vickhoff et al., 2013) found that singing had a positive effect on cardiovascular activity. Another study (Tarr, Launay, & Dunbar, 2014) found that singing has a strong effect on social bonding. A third study (Osman, Tischler, & Schneider, 2016) examined a singing group intervention for people with dementia and their caregivers, and found that patients experienced improvement in memory, both patients and carriers had betterment in their mood and relationship. Dassa and Amir (2014) found that music therapy with songs from the past of AD patients provided them with access to memories that led to spontaneous conversations. Patients also reported that they had a positive sense of well-being, belonging and a sense of achievement after music lessons. However, the above-mentioned studies all looked at people in late stages of AD.

A study (Hsieh, Hornberger, Piguet, & Hodges, 2011) found that despite severe impairment of episodic (and moderate impairment of semantic) memory, some patients with AD have nearly-preserved memory of musical information. In a study by Vanstone et al. (2012) five out of twelve patients with moderate or severe AD performed as well as the healthy control group in tests such as distinguishing familiar from novel melodies, identifying distortions in melodies, and singing familiar tunes. Another study (Cuddy et al., 2012) showed that long-term familiarity for melody was preserved across levels of AD (mild, moderate, and severe), and that the ability to sing a melody when prompted by its lyrics was retained at the mild stage and by a few individuals even through the severe stages of AD. Thus, musical semantic memory may be spared through the mild and moderate stages of AD and may be preserved even in some individuals at the late stage. A case study (Moussard, Bigand, Belleville, & Peretz, 2012) with a mild AD patient reported that learning of sung lyrics (even on unfamiliar melodies) led to better retention of words in AD patients. This finding is consistent with evidence (El Haj, Clément, Fasotti, & Allain, 2013) suggesting that relatively brief exposure of AD patients to music (such as listening to music for a few minutes) has effects on language production in terms of fewer empty words, higher grammatical complexity and pro-positional density. In addition, brief music exposure has beneficial effects on episodic memory retrieval (Foster & Valentine, 2001; Irish et al., 2006) even if the music is unrelated to the recalled autobiographical event (El Haj, Postal, & Allain, 2012). One of the reasons why musical interventions work well for older patients with AD is that musical memory is relatively intact (Jacobsen et al., 2015). Another study (Oostendorp & Montel, 2014) found that older AD patients could learn and remember new information with singing, despite suffering from severe memory loss. The authors suggested that future research should look at whether singing can prevent memory loss for individuals with AD in earlier stages of the disease.

The findings above indicate that memory for musical information is less impaired than episodic and semantic memory in AD patients (whether musical memory is represented as music-semantic memory, or procedural memory, or both). Moreover, the findings suggest that activations of representations of musical memory can lead to benefits in the domains of episodic and semantic memory retrieval, as well as in the domain of language production. The notion of a separate musical memory that can exert positive effects on episodic and semantic memory impairment is consistent with a recent case study (Finke, Esfahani, & Ploner, 2012) of a 68-year-old professional cellist who developed severe amnesia following encephalitis: Despite severe semantic and episodic memory impairments, this patient performed like healthy musicians in various tests of recognition memory for music. Moreover, the patient was strikingly unimpaired in the learning and retention of new musical information (despite severe impairment in learning, e.g., new faces). The authors concluded that “learning and retention of musical information depends on brain networks distinct from those involved in other types of episodic and semantic memory”, and that “learning and memory of complex musical information constitute an island of intact cognition within a severe amnesic syndrome.” (Finke et al., 2012).

Music and emotion in AD. In addition to memory- and language-related phenomena, music can aid to reduce anxiety and depression of AD patients. For example, a randomised controlled trial (Guetin et al., 2009) suggests that patients with mild to moderate AD show a reduction of anxiety and depression scores over the course of weekly sessions of receptive music therapy (compared to a reading group). This finding is consistent with several recent meta-analyses on effects of music therapy in AD patients. However, all of these meta-analyses (McDermott, Crellin, Ridder, & Orrell, 2013; Ueda, Suzukamo, Sato, & Izumi, 2013; Vink, Bruinsma, & Scholten, 2003; Wall & Duffy, 2010) also noted that the methodological quality of studies was low. For example, Ueda et al. (2013) concluded that “it seemed that depression and anxiety were reduced in the patients with the Alzheimer’s type of dementia, but the number of studies was insufficient to establish an effect on this type of dementia”. Similarly, McDermott et al. (2013) concluded that “Evidence for short-term improvement in mood and reduction in behavioural disturbance was consistent, but there were no high-quality longitudinal studies that demonstrated long-term benefits of music therapy.” Wall & Duffy (2010) reported positive increase in participants' mood and socialization skills across studies, but also noted that “methodological limitations were apparent throughout each of the studies reviewed”, and recommended “the undertaking of further research to explore the effects of music therapy on the behaviour and wellbeing of older people with dementia.” For the present study it is worth noting that no previous study investigated AD patients who had already learned an instrument (e.g., during childhood and adolescence); however, active music making in the form of singing has been applied in a few studies, and the meta-analysis by McDermott et al. (2013) found that “singing featured as an important medium for change.” A meta-analysis (Fusar-Poli, Bieleninik, Brondino, Chen, & Gold, 2017) found that music therapy is important as a complimentary treatment for older adults with dementia; specifically, the review found that active (music making) but not receptive methods (music listening) had a beneficial effect on cognitive abilities; subgroup analysis found evidence of a beneficial effect of active MT on global cognition (SMD = 0.29, 95% CI 0.02 to 0.57,  $p = 0.04$ ). Thus, there are hints that active music making (as planned in the present study) may be more beneficial than simply listening to music.

Interaction of memory functions with music-evoked emotions is plausible due to the co-localization of memory functions and emotion in the hippocampus. In a recent review (Koelsch, 2014) the applicant showed that music-evoked emotions involve the hippocampal formation across several studies (beyond neural systems involved in reward and pleasure). Moreover, recent research (Jacobsen et al., 2015; Pantev & Herholz, 2011) suggests that brain areas underlying musical memory are among the last to show atrophy in AD patients.

Theoretical models for beneficial effects of music in AD. There is also a paucity of theoretical models underlying effects of music in AD patients. Thus, many previous studies (McDermott et al., 2013) suffer from weak motivation for using music and lacking definitions of outcome measures. Moreover, due to the lack of theoretical models, there is a lack of systematic evidence for different factors that might contribute to beneficial effects, including the well-being of dementia patients. The present project aims at identifying such factors (see next section), thus also establishing a new theoretical basis for MT research with dementia patients.

The strong effects of music, in particular music making, on brain plasticity have been shown in a plethora of neuroscientific studies with both healthy individuals (Jäncke, 2009; Münte, Altenmüller, & Jäncke, 2002) and patients (Särkämö et al., 2008). A study used functional magnetic resonance imaging technique (fMRI) (Satoh et al., 2015) and AD patients underwent music therapy sessions once a week for six months. After six months, patients had increased activity in right angular gyrus and left lingual gyrus and they did better on cognitive processing exercises. In England a study (Skingley, Martin, & Clift, 2016) where elderly people sing in groups together, participants experienced improved well-being and health.

Research has shown that it is possible to prevent falls by exercising. An alternative intervention, which is helpful for the users, is exercise. There has been research on dementia and effects of exercise (Hulme et al., 2010) where training were considered an effective non-medical treatment compared to other non-medical treatments. In Bergen Municipality's report "Safe on Two Legs" Bergen Kommune (2010) reported that balance training and strength have the best results for preventing falls. In the report, more studies (Campbell, Robertson, Gardner, Norton, & Buchner, 1999; Helbostad, Leirfall, Moe-Nilssen, & Sletvold, 2007; Skelton, Dinan, Campbell, & Rutherford, 2005) displayed how inactive seniors who had not previously experienced falls had a good effect of one year's training. The training group reduced the number of falls by 30% compared with the control group. The effect of exercise was also greatest in the elderly with initial or established functional failure. People with Alzheimer's have functional failure of cognitive functions, languages, and the like. According to the Safe on Two Legs report (2010), muscle strength is the low-impact effect a muscle or muscle-group can develop. Muscle strength is something that decays when people get older, and the average muscle density of a person in their 60s is about 40% less than in a 20-year-old. In an article (Liu & Latham, 2009), it appears that elders that exercise strength become stronger and achieve better function in daily activities. Another study (Kalapotharakos, Michalopoulos, Tokmakidis, Godolias, & Gourgoulis, 2005) showed that two groups of elderly people who did use to exercise did better on functional tests after a training intervention. According to the Bergen Commune report, exercise for the elderly as for young people must be done 2-3 times a week with a certain intensity (8-12 repetitions and 3 sets) and be done for a minimum duration of 12 weeks to have an effect (2010).

The reason we want to do our study is the lack of good evidence-based qualitative research in the field of music therapy and neuroscience. Most of the research on AD patients is done in later stages of the disease, and it has been recommended to try and look at music intervention as a prevention of deterioration in AD. Therefore the current project will investigate the effect of music intervention on AD patients in early stages of the disease.

### **Specific Objectives**

The purpose of the project is to improve health for patients who are in an early stage of Alzheimer's disease (AD). It is expensive for the municipality with nursing homes, and the goal of the project is to find a therapy that can keep people with AD at home as long as possible. The aim is also to increase the quality of life in AD patients. Scientifically, the purpose is to look at changes in the

mind of persons with AD, who undergo a music intervention, compared with AD patients who do not undergo a music intervention.

### **Research Questions**

1. How does the brain change after a music intervention for patients with AD, compared to other AD patients who have not received a music intervention?
2. How does depression severity change in patients with Alzheimer's in the various intervention groups?
3. Can song training stop natural disease progress in patients with AD?
4. Is there a difference in the brain of a group that gets a music intervention compared to a group that does not receive music intervention for patients with AD?
5. How do cognitive functions like attention, language and memory change after a song intervention on patients with AD?

### **Trial Design and Rationale**

A quantitative design has been selected for the possibility of generalisation. Functional Magnetic resonance imaging technique (fMRI), diffusion tensor imaging (DTI) and magnetic resonance data will be retrieved from patients to measure brain-plasticity before and after music intervention. Neurological tests will be conducted to measure cognitive, social and motor functions before and after the intervention. Data will be collected by competent staff. The interventions will be performed by competent staff, respectively, vocal teachers, conductors, music therapists, physiotherapists and occupational therapists.

### **Trial Design**

This is a parallel, three-arm, single-blind (assessor-blinded) randomised controlled trial. Participants will be randomised to either a music intervention (singing lessons), a non-musical training intervention or no intervention. To ensure allocation concealment, the randomisation list will be created and kept at an external research office at Uni Research, by researchers who have no direct involvement with the clinical work.

## **Methods**

### **Study Setting**

Data will be collected in Bergen Norway, at the university hospital Haukeland or at the IBMP which is located behind Haukeland and is considered part of the university of Bergen, as well as part of the university hospital.

After discussions with health professionals in the Bergens area, it is already assumed that we have to recruit from day centers in and around Bergen, such as Askøy, Sotra, Øygarden, Os and others. Sogn og Fjordane is also potential place for recruitment.

### **Eligibility Criteria**

All adults with AD, above the age of 18, of any gender, are eligible to participate. In addition to having a diagnosis of AD, participants must live at home (not in a residential aged care facility, however they may have plans to move to such a facility in the future) and be able to give informed consent for the study. They also need to be able to complete questionnaires in Norwegian, to undergo magnetic resonance scans, and to attend intervention and assessment sessions in the area of Bergen, Norway. Participants can be non-musicians, amateur/hobby musicians, or professional musicians.

If participants move to a nursing home during the intervention period, they will not be excluded. All participants randomised will be retained and analysed, according to the intention-to-treat principle (see Statistical analyses).

## **Exclusion Criteria**

Participants with hearing impairments that cannot be mended by hearing aids will be excluded due to the importance of listening. Participants with claustrophobia and metal operated into the body, such as a pacemaker, will not be able to participate as that would make it impossible to gather fMRI data.

## **Interventions**

All will be provided by appropriately qualified personell, but may be provided by advanced students under supervision of a qualified professional. Singing lessons will be provided once a week for a period of 12 months by a person with a qualification in music therapy, or by a person with a different relevant qualification (e.g. psychology and music teaching) under the supervision of a music therapist. Exercise will be provided by a occupational therapists or a physiotherapist or students under supervision.

## **Music Intervention**

The music intervention consists of singing lessons and choir practice. Singing lessons will take place once a week for each participant every week for about 12 months. The therapist will come home to the participant, or meet them at the day centre and similar places. Participants will be given CD or MP3 files (as they prefer) with audio files with warm-up exercises, play songs and the song they will learn with their voice. Self-produced music material from the institute will be given to the participants in a media format they prefer. Example material can be found here: <https://soundcloud.com/[name]/jeg-gikk-en-tur-pa-stien> All participants in the music intervention group will meet one to two times a month to sing the songs they have learned in the individual singing lessons together in a choir. The choir will take place in at a place devised by Bergen Municipality. The intervention is standardised (see Appendix A for a detailed schedule), but therapists are free to make small changes to adapt the individual.

## **Exercise Intervention**

The exercise group will have similar arrangements, but meet once a week for a group training session rather than individual hours once a week. At the same time they will also be followed by a personal physiotherapist or occupational therapist before the training intervention begins and after. They will also offer group tours, such as mountain hikes and the like twice a month. We will base the training offer on the program «Trygg på to bein» by Bergen municipality (2010) intended for the elderly. The training will take place outdoors and at Bergen Municipality owned house. The intervention is quite standardised, but therapists are free to make small changes to adapt the

individual. Different from “safe on two legs”, this intervention will not use music during training sessions (see Appendix B). It will also be tailored to enable participation of all included participants.

## **Control Intervention**

The control group will continue on medications and activities that they usually have. They will not be asked to quit training or music if they are currently participating in such activities.

## **Assessment of Attendance and Fidelity**

Participation in the program will be documented by the therapists in charge of the intervention by simply marking if the participants attend the intervention. 80 % participation is required for inclusion in analysis.

Mid intervention we will also interview participants about how they like their therapist and the therapy, and if they are doing the interventions on their own at home. However, there will be no strict measures of whether they do the intervention on their own. This is encouraged, but not a must.

There will be a midway evaluation of therapists for both the active interventions. Here we will inquire if they overlapped in any way. Both will be asked the same questions:

«Did you use music?», «Did you use exercise?»

Then we will ask the participants the same questions about the therapy sessions. This includes double self-reports from therapists and participants. In addition we will ask participants for their compliance, or how much they practiced on their own.

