## **Statistical Methods**

All primary analysis will be conducted in the modified intention-to-treat population, i.e. all who were randomised and for whom outcome data are available will be analysed in the group to which they were randomised, regardless of whether they received the full intended intervention. All continuous variables will be screened for normality of distributions. If normality is confirmed, the three interventions will be tested in an overall test (one-way ANOVA with three levels), followed by multiplicity-adjusted post-hoc t-tests (as described in Statistical analyses below). However, only one comparison – music intervention versus standard care – is regarded as the primary comparison. Multiplicity adjustment is made for the two primary outcomes, leading to a two-sided 2.5% significance level. All other comparisons and outcomes are regarded as exploratory secondary and are not multiplicity-adjusted (i.e. will be tested on a two-sided 5% level). Additional sensitivity analyses will be conducted on the per-protocol population (by treatment received). Subgroups such as gender, education will also be investigated. Adjusted measures will be music aptitude at baseline. Working alliance will be examined as a mediator variable of later clinical outcomes.

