## Ethics and Dissemination

### **Ethical Challenges**

The current study is investigating an exposed group, people who have Alzheimer's disease. Even at an early stage in the disease, this group may be considered exposed. For the current study it is important that participants are living at home and the interventions may help them stay home longer. Music and exercise have the health and positive effects on patients with AD, but also generally older people and their caregivers. Nevertheless, there is little high quality research on long-term music and exercise therapy in people with AD. Therefore, this study holds great potential; it is an exploratory study. Little suggests negative effects of song and exercise in people with AD. The literature states that depression and anxiety decreases with music therapy, and well-being increases, but no evidence suggests a stop of disease progression.

The group may not continue to stay home during the intervention, the literature states that depression, anxiety decreases with music therapy, and well-being increases, but it is no evidence that suggests a stop of disease progression. We assume new learning and active use of hippocampus may have positive effects on the brain. If participants move away from home during the period, they will continue to receive the same offers from us. We expect some dropouts from the study, hence we want to test as many patients as possible. If participants no longer wish to do the intervention, but still want to be tested, that will be allowed. If participants wish to do the intervention, but not be tested they will be allowed to do that as well.

fMRI and MR may be experienced as uncomfortable by some participants, but are necessary for the research, however it is not dangerous for the participants.

Retrieval of personal data and neuropsychological tests can also be uncomfortable for some of the participants, but where a computer can be utilized, it will, to limit researcher access and vulnerability of participants.

Music therapy or exercise may not be attractive to everyone. Song has ecological validity in our everyday lives. We humans often meet and sing in different contexts, such as for weddings, funerals, in church, at work and school. We will also ask participants what they prefer of singing,

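### The 80% attendance rule names no analysis set and contradicts the protocol's own primary analysis population; it should be confined to the per-protocol sensitivity analysis

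*Protocol*

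**What the plan says.** Four parts of the protocol decide who is analysed.

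- **Assessment of Attendance and Fidelity:** "80 % participation is required for inclusion in analysis". The sentence does not say which analysis it means. On recording, the same section says "Participation in the program will be documented by the therapists in charge of the intervention".
- **Eligibility Criteria:** "All participants randomised will be retained and analysed, according to the intention-to-treat principle", with a pointer to the statistical section.
- **Statistical Methods:** for all primary analysis, "all who were randomised and for whom outcome data are available will be analysed in the group to which they were randomised", and this holds "regardless of whether they received the full intended intervention". A second population appears only for sensitivity: "Additional sensitivity analyses will be conducted on the per-protocol population (by treatment received"). No attendance threshold is given there.
- **Ethical Challenges:** "If participants no longer wish to do the intervention, but still want to be tested, that will be allowed".

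On the comparator, Control Intervention says "The control group will continue on medications and activities that they usually have". Statistical Methods makes music versus standard care the one primary comparison, tested at a two-sided 2.5% level for each of two primary outcomes.

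**The concern.** Read literally, the attendance sentence and the primary population cannot both be followed. Someone in the music arm who attends 60% of lessons and returns for the 12-month scan and depression scale is excluded by the first and included by the second. Such people can exist, because the protocol lets participants stop the intervention and still be tested.

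The rule also acts on one side only. Attendance is marked by the therapists who deliver the sessions, and the control arm has none. Applied to music versus standard care, it would select one arm on something that happens after randomisation and leave the other arm whole. If attendance is related to how participants fare, the difference between arms would then partly reflect that selection. Even if it is not, the music arm would lose numbers.

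**Working it through.** **1. The plan's own figure.** Inputs from Sample Size: d = 0.7, two-sided 2.5%, 40 per group, 80% power. The normal approximation gives 39 per group. The exact two-sample t-test has noncentrality d / √(1/n₁ + 1/n₂) = 0.7 / √(1/40 + 1/40) = 3.130 on 78 df, and power 79.9%. The stated 40 per group is reproduced. The recruitment target of 45 allows 1 − 40/45 = 11.1% for attrition.

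**2. The sections side by side, for a music participant below 80% attendance with 12-month data.**

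| Section | In the analysis? |
|---|---|
| Eligibility Criteria | Yes |
| Statistical Methods, primary analysis | Yes, whatever intervention was received |
| Assessment of Attendance and Fidelity | No |

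For a control participant with 12-month data the attendance rule has nothing to act on.

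**3. What the rule would do to the primary comparison if it were applied.** Two figures are needed that the protocol does not give: the share f of the music arm below 80%, and the correlation ρ between attendance and a good outcome. Both are assumed here. Under a normal model with no true effect, removing the lowest-attending share f from the music arm only gives

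bias in SD = ρ · φ(q) / (1 − f), where q is the f-quantile of the standard normal.

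- f = 10%, ρ = 0.1: q = −1.282, φ(q) = 0.1755, bias = 0.1 × 0.1755 / 0.9 = 0.02 SD.
- f = 20%, ρ = 0.3: q = −0.842, φ(q) = 0.2800, bias = 0.3 × 0.2800 / 0.8 = 0.105 SD.
- f = 30%, ρ = 0.3: q = −0.524, φ(q) = 0.3477, bias = 0.3 × 0.3477 / 0.7 = 0.149 SD, or 21% of d = 0.7.
- Any f, ρ = 0: bias = 0.

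Over f = 10–40% and ρ = 0.1–0.5 the bias runs from 0.02 to 0.32 SD.

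Simulated type I error of the two-sided 2.5% t-test, no true effect:
- 10% excluded, ρ = 0.1, 40 per arm: about 2.6%.
- 20% excluded, ρ = 0.3, 40 per arm: 3.8%.
- 30% excluded, ρ = 0.3: 5.2% with 40 per arm, about 5.5 to 6% with 45 per arm.
- 30% excluded, ρ = 0: nominal within simulation error (2.4 to 2.6%).

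**4. Power at d = 0.7 from the reduced music arm, without bias.**

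| Music vs control | Noncentrality | Power |
|---|---|---|
| 40 vs 40 (as planned) | 3.130 | 79.9% |
| 36 vs 45 (20% of 45 excluded) | 0.7 / √(1/36 + 1/45) = 3.130 | 79.9% |
| 31 vs 45 (about 30% of 45 excluded) | 0.7 / √(1/31 + 1/45) = 2.999 | 76.0% |
| 30 vs 40 (25% excluded after full attrition) | 0.7 / √(1/30 + 1/40) = 2.898 | 72.7% |

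**The case against.** The strongest reply is that the attendance sentence sits in a fidelity section, while Statistical Methods, the section meant to govern, explicitly disregards the amount of intervention received in all primary analysis. The only population there that depends on treatment delivery is the per-protocol one, so the 80% figure was probably meant as its threshold. This is the natural reading, but the protocol does not state it: the attendance sentence is unqualified, and the per-protocol set is described without a threshold. The contradiction in the text stands.

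The reply does limit how far the point goes. A reader might infer any of the following; the protocol does not support them.

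- **That the primary comparison will be biased in favour of music.** This needs the attendance sentence to override Statistical Methods and attendance to be linked with good outcome. A link through disease progression or mood is plausible, but nothing in the protocol establishes it. Lessons can take place at home or at the day centre, and people who move to a nursing home keep the same offers, both of which may weaken it.
- **That Eligibility Criteria and Statistical Methods form a further conflict.** The first states a principle and refers onward; the second makes it operational by requiring outcome data. The difference is slight and does not bear on attendance.
- **That controls who sing or train would be moved to another arm.** The bracketed phrase about treatment received is loose, but nothing says controls would be reassigned, and it concerns sensitivity analyses only.
- **That power must fall below plan.** At 36 vs 45 it equals the planned 79.9%. Low attenders and dropouts may also be partly the same people, so adding the two losses can count some twice.

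**Conclusion.** Wrong as written. The attendance rule contradicts the primary analysis population in Statistical Methods and the intention-to-treat statement in Eligibility Criteria, and it can act only on the active arms. Both facts follow from the text and need no assumption.

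The numerical consequence is conditional: it arises only if the rule is applied to the primary comparison, and its size and direction rest on an assumed share below 80% and an assumed correlation. Plausible inputs run from negligible to a type I error more than twice the nominal 2.5%. If Statistical Methods is followed, the stated design is unaffected. The contradiction should nevertheless be removed in advance, because participants know their allocation and the depression scale is self-reported, so a choice of analysis set made after the data are seen would be hard to defend.

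**What to change.** In Assessment of Attendance and Fidelity, state that the 80% threshold does not apply to the primary analysis and serves only to define the per-protocol sensitivity set. Leave the primary analysis as Statistical Methods has it: participants with outcome data, in the arm to which they were randomised, whatever their attendance.

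In Statistical Methods, replace the bracketed description of the per-protocol set with a definition by assigned arm: music and exercise participants with at least 80% attendance, and all controls with outcome data. Because that set remains selected in the active arms only, report it as supportive.

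The cost is a few sentences in the protocol, carried into the statistical analysis plan. No new data, assessments or participants are needed.
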